## **G. Statistical Analysis**

Continuous variables were presented as mean (SD) or median (interquartile range, [IQR]), depending on whether the data was distributed normally or not. Categorical variables were presented as a number (percentage). The normal distribution of data was evaluated using the Shapiro–Wilk test, and the Levene method was used to test the homogeneity of variance. Differences in repeated measures variables were analyzed by repeated-measures analysis of variance. Continuous outcomes were analyzed with one-way analysis of variance (ANOVA) or Kruskal-Wallis test. Categorical variables were tested using  $\chi^2$  test or Fisher's exact test. Time-to-event outcomes were illustrated using Kaplan-Meier curves. For a post hoc sensitivity analysis, we employed a logistic regression model. Statistical significance was defined as  $P < 0.05$ . Statistical analysis was conducted using SPSS v27.0 (SPSS Inc., Chicago, IL, USA).

## **H. Intervention and Study Procedures**

During the access procedure, we adjust the patient to a supine position with a slight external rotation of the hips (the "frog-legged" position). Landmarks such as the anterior superior iliac spine, pubic symphysis, and inguinal ligament were identified. The femoral artery pulse was palpated 2-3 cm below the midpoint of the inguinal ligament and puncture was performed at 1-2 cm medial to the femoral artery. After sterile prep and a small subcutaneous dose of lidocaine, the needle was inserted steeply downward at a 30°-45° angle into the skin in different directions according to the patient's grouping and the timer was initiated. Crossover to the ultrasound-guided puncture occurred after three unsuccessful attempts. The timer was stopped when the puncture needle entered the target vessel or after three unsuccessful attempts. All patients underwent a puncture of the right femoral vein in this study.

Based on the relationship between the femoral vein and artery, Guan et al. classified the anatomy into four types (Fig. 3): Type I (vein parallel to artery without overlap),

Type II (vein medial to artery with lumen overlap  $\leq 50\%$ ), Type III (vein posterior to artery with lumen overlap  $> 50\%$ ), and Type IV (vein lateral to artery) [9]. After the puncture catheterization, vascular ultrasonography was used to evaluate the femoral vasculature anatomy in the puncture area of each patient.

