## **E. Randomization and Blinding**

Randomization was performed using a computer-generated random numbers table with a 1:1 allocation ratio. The allocation sequence was sequentially numbered and sealed in opaque envelopes by the corresponding author. The anesthesiologists opened the envelopes 10 minutes before the procedure commenced. Due to the nature of the intervention, full blinding of all study personnel was not feasible. However, to minimize bias, we attempted to blind the patients, research assistants, and data analysts. To achieve patient blinding, during the informed consent process, we described all interventions as femoral vein catheterization, and we explained that depending on group allocation, patients might receive different puncture trajectories.

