## **I. Measurements and Endpoints**

The following parameters were systematically recorded for all enrolled patients:

(1) First-attempt Success Rate: Defined as the successful aspiration of venous blood through the needle on the initial skin puncture, without any needle withdrawal or redirection. This metric primarily reflects the precision of the initial puncture technique.

(2) Overall Success Rate: Defined as the ultimate successful aspiration of venous blood, achieved within a maximum of three puncture attempts or before the occurrence of any significant complication necessitating termination of the procedure.

(3) Number of Puncture Attempts: This refers to the total count of separate skin punctures required to achieve successful venous blood aspiration. Each withdrawal of the needle tip completely from the skin followed by a new puncture constitutes a new attempt. Minor redirections of the needle beneath the skin without complete withdrawal are not counted as separate attempts.

(4) Puncture Time: Measured in seconds, from the moment the needle first touches the skin until the successful aspiration of venous blood. The timer is stopped immediately upon confirmation of free venous blood flow into the syringe.

(5) Procedure-related Complications: All adverse events occurring during or immediately after the puncture procedure were meticulously documented. These include, but are not limited to accidental arterial puncture, hematoma formation, pneumothorax, etc.

(6) Anatomic Relationship between the Femoral Vein and Artery.

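### Haematoma has no stated detection method, criterion or assessor, and the ultrasound already done in every patient is not stated to record it

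*Protocol*

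**What the plan says.** Four statements in the protocol bear on this point.

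- **The scan (section III.H).** "After the puncture catheterization, vascular ultrasonography was used to evaluate the femoral vasculature anatomy in the puncture area of each patient". It covers all patients in both arms. The stated purpose is the four-type classification of vein and artery, which serves item (6) of section III.I, "Anatomic Relationship between the Femoral Vein and Artery". The timing is given only as after catheterisation.
- **The complication endpoint (section III.I, item 5).** "All adverse events occurring during or immediately after the puncture procedure were meticulously documented". The next sentence gives the examples: "These include, but are not limited to accidental arterial puncture, hematoma formation, pneumothorax, etc". Unlike items (1) to (4) of the same section, which have working definitions, item (5) gives no criterion for haematoma, no method of detection and no assessor.
- **Knowledge of the arm (section III.E).** "The anesthesiologists opened the envelopes 10 minutes before the procedure commenced", and "Due to the nature of the intervention, full blinding of all study personnel was not feasible".
- **Blinding attempted (section III.E).** "we attempted to blind the patients, research assistants, and data analysts". The section does not say that any of these people record complications or perform the scan.

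Safety is part of the objective (section I), and the incidence of immediate complications is named as a key outcome (section II.C).

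**The concern.** The trial compares two needle directions from the same medial starting point, and the newer one is angled towards the femoral artery (section II.B). The same section expects this direction to lower the number of attempts and the complications that go with them. Haematoma is therefore a central safety question for the comparison.

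Without a criterion, a method or a named assessor, whether a swelling is written down as a haematoma is left to judgement. The operators know the arm, and nobody unaware of it is given the task. If the two arms were not observed in the same way, the reported rates would partly reflect the observing. Few events can be expected with 54 patients per group, so a handful of judgement calls would move the estimate visibly.

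Meanwhile every patient has an ultrasound of the puncture area after the procedure. Recording haematoma on it would give both arms the same examination at little cost, and the protocol does not say that this is done.

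**Working it through.** **1. What the plan fixes for each element of ascertainment**

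| Element | First-attempt success, item (1) | Haematoma, within item (5) | Vein-artery anatomy, item (6) |
|---|---|---|---|
| Criterion | Defined | Not stated | Four types, section III.H |
| Method | Venous aspiration | Not stated | Ultrasound in every patient |
| Time | First skin puncture | During or immediately after puncture | After catheterisation, no interval given |
| Assessor | Not stated | Not stated | Not stated |
| Assessor unaware of arm | Not stated | Not stated | Not stated |

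The scan and the haematoma endpoint concern the same region in the same patients, and their time windows can be made to agree. The protocol does not connect them.

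**2. Figures available**

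The plan gives no haematoma rate, so there is no figure of its own to reproduce on this point. The one figure used below is the 54 per group in section III.F. Its base of 42 reproduces: 90% against 60%, two-sided 0.05, power 0.9, pooled normal approximation without continuity correction gives 42. Inflating for 20% attrition gives 42 / 0.8 = 52.5, so 53 against the stated 54. The sample size rests on puncture success, and this point does not touch it.

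**3. Illustration of differential detection (rates assumed)**

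Assume a true haematoma rate of 10% in both arms: 0.10 × 54 = 5.4 per arm.

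| Detection assumed | Lateral-medial arm | Medial-parallel arm |
|---|---|---|
| Complete in both | 5.4 (10%) | 5.4 (10%) |
| Half missed in the lateral-medial arm only | 2.7 (5%) | 5.4 (10%) |
| Half missed in the medial-parallel arm only | 5.4 (10%) | 2.7 (5%) |
| Half missed in both | 2.7 (5%) | 2.7 (5%) |

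One-sided under-detection halves or doubles the apparent ratio, depending on the arm. Equal under-detection creates no difference when the true rates are equal. The protocol does not allow a choice between these rows.

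**4. Would such a difference look like a finding?**

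In whole patients, 3/54 against 5/54 gives a two-sided Fisher p of 0.72, and 3/54 against 6/54 gives 0.49. Neither would be declared significant.

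Power with n = 54 per group, from Φ{(|p1 − p2|√n − 1.96√[2p̄(1 − p̄)]) / √[p1(1 − p1) + p2(1 − p2)]}:

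- 5% against 10%: (0.05 × 7.348 − 1.96 × 0.3725) / 0.3708 = (0.367 − 0.730) / 0.3708 = −0.98, so about 16%.
- 10% against 20%: about 31%.
- 5% against 15%: about 41%.

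The haematoma comparison will mainly be read as an estimate, and an estimate based on so few events is sensitive to two or three classifications.

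**The case against.** The strongest reply is that much of the case rests on silence, and several tempting inferences go beyond the text.

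- **That the operator records haematoma.** A reader might infer this because the operator is at the bedside. Item (5) is in the passive and names nobody. Research assistants, whom the trial tried to blind, may be the recorders. What stands is that no assessor is stated.
- **That a haematoma seen on the scan is thrown away.** Section III.H gives one purpose and excludes no other, and item (5) does not bar scan findings from the record. What stands is that recording them is not required.
- **That the scan takes place at the moment complications are assessed.** The text says only that it follows catheterisation. What stands is that the time needs fixing.
- **That bedside inspection misses haematomas.** The protocol neither says so nor says that inspection is the method. The point does not need this premise.
- **That any bias would favour the new direction.** The direction is unknown, equal under-detection fits the text just as well, and the illustrated differences are far from significance.

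Two practical objections stand and limit the fix. Replacing a clinical endpoint with an imaging one is debatable, because some scan-detected haematomas will have uncertain clinical relevance. Also, under section III.H patients with three failed attempts cross over to ultrasound-guided puncture, so a scan after catheterisation can show haematoma from those later punctures, possibly unequally by arm.

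The general undertaking in section IV to record adverse events in detail does not answer the point, since it gives neither a haematoma criterion nor an assessor. The methods are mostly in the past tense, so the change may come too late for patients already scanned.

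**Conclusion.** The point holds as a weakness in how a named safety outcome is measured. It is not an internal contradiction, and neither the sample size nor the puncture-success comparison is affected. The protocol fixes no criterion, method or assessor for haematoma, leaves operators aware of the arm, and does not state that the universal post-procedure scan records it. Ascertainment could differ by arm. Direction and size are unknown, and the documents do not show that it does differ. The 5% against 10% example shows only how few patients are needed to move the estimate; it rests on an assumed 10% rate and an assumed miss of half the cases in one arm. The remedy is worth making because it is uniform across arms and adds no procedure. It is an improvement and not a condition for the trial's validity.

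**What to change.** Amend sections III.H and III.I (items 5 and 6) as follows.

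1. State that the existing post-catheterisation scan also records haematoma, present or absent, with its largest diameter, on one form used in both arms.
2. State the time after the procedure at which the scan is done.
3. Where existing staff allow, whoever already does the scan should be someone other than the operator and should not be told the arm. A separate reader need not be required. If research assistants unaware of the arm already record complications, say so in section III.E.
4. Report scan-detected haematoma by arm beside the clinically observed haematoma, without replacing it.
5. Flag patients who crossed over to ultrasound-guided puncture, so that haematoma possibly due to the later punctures can be identified.

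If scans are already complete, any stored images could be read for haematoma without knowledge of the arm. If none were stored, the limitation should be declared.

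Cost: one or two form fields on a scan already done, a stated scan time, and some attention to who performs it. Recorded haematoma rates will probably rise in both arms, and some of the added cases will be of uncertain clinical relevance.

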## **I. Measurements and Endpoints**

The following parameters were systematically recorded for all enrolled patients:

(1) First-attempt Success Rate: Defined as the successful aspiration of venous blood through the needle on the initial skin puncture, without any needle withdrawal or redirection. This metric primarily reflects the precision of the initial puncture technique.

(2) Overall Success Rate: Defined as the ultimate successful aspiration of venous blood, achieved within a maximum of three puncture attempts or before the occurrence of any significant complication necessitating termination of the procedure.

(3) Number of Puncture Attempts: This refers to the total count of separate skin punctures required to achieve successful venous blood aspiration. Each withdrawal of the needle tip completely from the skin followed by a new puncture constitutes a new attempt. Minor redirections of the needle beneath the skin without complete withdrawal are not counted as separate attempts.

(4) Puncture Time: Measured in seconds, from the moment the needle first touches the skin until the successful aspiration of venous blood. The timer is stopped immediately upon confirmation of free venous blood flow into the syringe.

(5) Procedure-related Complications: All adverse events occurring during or immediately after the puncture procedure were meticulously documented. These include, but are not limited to accidental arterial puncture, hematoma formation, pneumothorax, etc.

(6) Anatomic Relationship between the Femoral Vein and Artery.

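### Puncture time and number of attempts are defined only for successful punctures, which conflicts with the timer rule and leaves failures without a value in the comparison

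*Protocol*

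**What the plan says.** Section III.I of the protocol opens with "The following parameters were systematically recorded for all enrolled patients". Item (4) then gives puncture time as "Measured in seconds, from the moment the needle first touches the skin until the successful aspiration of venous blood", and adds: "The timer is stopped immediately upon confirmation of free venous blood flow into the syringe". Item (3) defines the number of attempts: "This refers to the total count of separate skin punctures required to achieve successful venous blood aspiration".

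Section III.H has a different rule for the timer: "The timer was stopped when the puncture needle entered the target vessel or after three unsuccessful attempts". It also says what follows a failure: "Crossover to the ultrasound-guided puncture occurred after three unsuccessful attempts".

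Section III.G assigns the tests: "Continuous outcomes were analyzed with one-way analysis of variance (ANOVA) or Kruskal-Wallis test". On curves it says only "Time-to-event outcomes were illustrated using Kaplan-Meier curves", without naming an outcome, an event or a censoring rule.

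Section II.C lists both the number of attempts and procedural time among the key outcomes. No outcome is designated as primary.

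**The concern.** The statements cannot all hold. A patient with three failed attempts has no puncture time and no attempt count under III.I, has a stop time under III.H, and is supposed to have every parameter recorded. III.I item (2) also foresees stopping for a significant complication, and neither timer rule covers that case.

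The analyst has to choose, and the choice affects the result:

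- **Follow III.I literally.** Failures drop out. The arms being compared are then no longer the randomised arms but those who succeeded, and success is what the needle direction is meant to change. The arm with more failures loses its hardest patients.
- **Follow III.H.** Failures enter with the stop time as if it were a time to success. If they are given three attempts, they look the same as patients who succeeded on the third.

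A choice of this kind should be made in the plan, without sight of the results.

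**Working it through.** **Plan's own figure.** Section III.F assumes success of 90% and 60%, two-sided 0.05 and power 0.90. With pooled variance and mean proportion 0.75:

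n = [1.960 × √(2 × 0.75 × 0.25) + 1.282 × √(0.90 × 0.10 + 0.60 × 0.40)]² / 0.30² = (1.200 + 0.736)² / 0.09 ≈ 41.7, so 42 per group, as stated. Inflating for 20% attrition gives 42 / 0.8 = 52.5, so 53 against the stated 54. This figure is not in dispute.

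**Expected failures.** III.F does not say whether 90% and 60% are first-attempt or overall rates, so both readings are shown, plus a third with strong anatomical variation. With constant per-attempt success p, the chance of three failures is (1 − p)³.

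- A, first-attempt rates: 0.1³ = 0.001 and 0.4³ = 0.064, or 0.1 and 3.5 failures of 54.
- B, overall rates: failure is 0.10 and 0.40, or 5.4 and 21.6 of 54. Per-attempt success is 1 − 0.10^(1/3) = 0.536 and 1 − 0.40^(1/3) = 0.263.
- C, heterogeneity (assumed): 40% deep veins, with per-attempt success in other and deep veins of 0.92 and 0.85 (lateral) and 0.90 and 0.15 (control). Control failure is 0.6 × 0.10³ + 0.4 × 0.85³ = 0.246, or 13.3 of 54. Lateral failure is 0.6 × 0.08³ + 0.4 × 0.15³ = 0.002, or 0.1 of 54. First-attempt success is about 89% and 60%.

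**Mean attempts, lateral vs control.**

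| Scenario | Successes only | Failures as 3 | Failures as 4 |
|---|---|---|---|
| A | 1.11 vs 1.46 | 1.11 vs 1.56 | 1.11 vs 1.62 |
| B | 1.53 vs 1.80 | 1.68 vs 2.28 | 1.78 vs 2.68 |
| C | 1.12 vs 1.27 | 1.12 vs 1.70 | 1.12 vs 1.94 |

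**Power for time.** Simulated Kruskal-Wallis test at the 0.05 level, 54 analysed per arm, with no attrition. Attempt times are assumed lognormal with median 20 s and log-SD 0.5. Rank-test power does not depend on the assumed median.

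| Scenario | Successes only | Failures at stop time | Failures ranked worst |
|---|---|---|---|
| A | 50% | 67% | 68% |
| B | 21% | 83% | 95% |
| C | 13% | 75% | 81% |

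Repeat runs moved these figures by about two percentage points at most. At a 20 s median, the difference in mean time is about 8 s among successes against 10 s with all timer values in A, and about 6 s against 14 s in B.

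**The case against.** The best defence reads the sections together. III.I covers all enrolled patients and III.H gives failures a stop time, so failures can be retained, and the protocol nowhere says they are excluded. On that reading the cost is small in A (67% against 68%) and moderate in B and C (83% against 95%, 75% against 81%). This stands as a limit on the size of the problem. It does not remove the conflict, because III.I still defines both measures so that a failure has no value. That is a defect in a definition, not detail left to an analysis plan.

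Three stronger conclusions might be inferred, and the documents do not support them:

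- **That the difference between techniques would vanish.** This comes close to true only under strong assumed heterogeneity or the overall-rate reading. In A, much of the difference survives. In all three scenarios the loss works against the arm with fewer failures, so it does not create a false advantage for the lateral approach.
- **That the Kaplan-Meier curves overstate success.** III.G names no outcome or censoring rule, and the curves only illustrate. If failures were censored at crossover, the control curve in C would read about 71% against a true 70% at 60 s, and 81% against 74% at 90 s. The large gap (above 90% against 75%) appears only at 200 s, where almost nobody is at risk. Overall success is in any case a separate endpoint.
- **That the selection is on the primary outcome.** None is designated.

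**Conclusion.** The concern holds in a limited form. III.H and III.I give different end points for one timer, and III.I leaves failures with no time and no attempt count. Dropping failures compares groups selected after randomisation and costs power for time in every scenario tried: from 68% to 50% at the mild end, from 95% to 21% on the overall-rate reading, and from 81% to 13% with marked heterogeneity. Keeping failures at their stop time costs far less, from about 1 to 12 percentage points.

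The direction is the same throughout. The size rests on assumed attempt times, on the per-attempt success pattern, and on which rate III.F means, none of which the protocol settles. The two success-rate endpoints and the sample size are not affected.

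**What to change.** 1. Reconcile the timer end points in III.H and III.I, and state which values are recorded for a failed or terminated procedure.
2. Analyse both outcomes in every randomised patient. Rank failures and terminated procedures worst: attempts coded above 3, time ranked after all successes. This needs only the fact of failure, so a missing stop time does no harm.
3. Compare the arms with the Kruskal-Wallis test already planned (with two arms, the rank-sum test), whatever the normality test shows, since a worst rank has no meaning in ANOVA.
4. Report time among successes as descriptive only, beside the number of failures in each arm.
5. If a time-to-success curve is drawn for puncture time, show the cumulative proportion succeeding, with failures kept in the denominator as never succeeding by the allocated technique, and not censored at crossover.

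The cost is wording, with no new data. The downside is that a worst-rank analysis gives no simple mean difference in seconds. Other rules that keep failures could also be defended, but one must be fixed without reference to the results.

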## **IV. DATE AND SAFETY MONITORING**

Clinical research will formulate a corresponding data safety monitoring plan according to the size of the risk. In the implementation stage of clinical research, record all adverse events in detail, handle and track them properly until they are properly resolved or the condition is stable, and report serious adverse events and unexpected events to the ethics committee, competent authorities and drug regulatory authorities in a timely manner as required; The principal investigator will periodically conduct a cumulative review of all adverse events, and if necessary, hold an investigator meeting to assess the risks and benefits of the study; We will arrange independent data monitors to monitor the research data, and high-risk studies will establish an independent data safety monitoring committee to monitor the accumulated safety data and efficacy data to make a decision on whether to continue the study.

